# Treatment outcomes of pulpotomy versus pulpectomy in vital primary molars diagnosed with symptomatic irreversible pulpitis: protocol for a non-inferiority randomised controlled trial

**DOI:** 10.1186/s12903-024-04411-6

**Published:** 2024-05-28

**Keywords:** Pulpectomy, Pulpotomy, Vital primary molars, Irreversible pulpitis

## Abstract

**Background:**

Pulpectomy continues to be the standard treatment recommendation for management of vital primary molars diagnosed with symptomatic irreversible pulpitis. The recent decade has seen a paradigm shift in the treatment concepts of how vital mature permanent molars diagnosed with irreversible pulpitis can be more conservatively managed using vital pulp therapy techniques like pulpotomy. However, despite emerging evidence indicating similarities between primary and permanent tooth pulp response to dental caries, there is limited research on whether pulpotomy can be similarly used as a definitive treatment modality for vital primary teeth with irreversible pulpitis. This randomised controlled trial (RCT) aims to compare the treatment effectiveness of pulpotomy versus pulpectomy in management of vital primary molars diagnosed with symptomatic irreversible pulpitis over a two-year period.

**Methods/design:**

This clinical study is a parallel, two-armed, open label, non-inferiority RCT with a 1:1 allocation ratio between the experimental intervention arm (pulpotomy) and the active comparator arm (pulpectomy). Healthy cooperative children, between 4–9 years of age, who have painful primary molars with clinical symptoms typical of irreversible pulpitis will be recruited after obtaining informed consent from their parents/legal guardians. 50 vital primary molars clinically diagnosed with symptomatic irreversible pulpitis will be randomly distributed between the two treatment arms. The primary outcomes that will be assessed are clinical and radiographic success after six-months, one-year and two-years of the trial interventions. The influence of baseline pre-operative variables (age; gender; tooth type; site of caries; pre-operative furcal radiolucency; pre-operative pain intensity) and intra-operative factors (time taken to achieve haemostasis) on treatment outcomes will also be assessed. The secondary outcome evaluated will be the immediate (24 h and 7 d) post-operative pain relief afforded by the two treatment interventions.

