### Objectives

Compare the treatment effectiveness of full pulpotomy vs. single-visit pulpectomy in the management of vital primary molars diagnosed with symptomatic irreversible pulpitis based on the clinical and radiographic outcomes of the treated teeth over a two-year period.Assess influence of baseline pre-operative variables (age; gender; tooth type; site of caries; pre-operative furcal radiolucency; pre-operative pain intensity) and intra-operative factors (time taken to achieve haemostasis) on treatment outcomes.

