### Follow-up timeline

Children enrolled in the study will be followed from the trial intervention until the end of the study (two years post-treatment). Trial participants and their parents/guardians will be initially contacted by phone 24 h after the treatment intervention to record their post-operative pain intensity score using the VAS. Post-operative pain intensity score will also be recorded 7 d after the treatment intervention before the placement of the SSC. Clinical and radiographic outcome data of the treated tooth will be recorded at 6 months, 12 months, and 24 months post-treatment. Children participating in the trial will be advised to continue their routine dental visits, with the recall period determined by their caries risk status. Any symptomatic visits to the dentist outside these follow-up timepoints will be identified and reason for the same recorded on the trial record form.

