### Trial outcomes

#### Primary outcomes

Clinical outcomes will be assessed by a single experienced paediatric dentist who shall be blinded to the treatment allocation. Radiographic outcomes will be assessed independently by two experienced paediatric dentists under optimum viewing conditions.

*Clinical success* of the treated tooth will be determined if all the following conditions are met:Absence of pain or discomfortAbsence of tenderness on percussion and palpationAbsence of any associated parulis/fistulaAbsence of any associated soft tissue swellingAbsence of any associated pathological mobility

*Radiographic success* will be determined as follows:Absence of pathosis on recall periapical radiograph i.e., no signs of pathological internal/external root resorption or new furcal/periapical lesions.Complete radiographic healing or reduction/no change in size of the any pre-operative furcal rarefaction. Teeth that show an increase in the size of any pre-operative furcal radiolucency will be considered as failed.

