### Target sample size

Sample size determination for this binary outcome non-inferiority randomised trial was calculated using a computer-generated system available online (https://www.sealedenvelope.com/power/binary-noninferior/). Based on previous clinical studies [29–31], a 95% success rate was assumed for both treatment interventions along with a 17% non-inferiority margin. Even an overall success rate of 78% for the experimental pulpotomy intervention would be considered non-inferior to the standard pulpectomy intervention. To obtain a power of 80% (β = 0.20) and a 2-sided α equal to 0.05, approximately 42 patients for both groups will be needed. To compensate for loss during follow-up and other causes of attrition, the targeted sample size will be 50 vital primary molar teeth diagnosed with irreversible pulpitis, distributed equally between the two trial treatment arms.

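### Six outcomes are called primary, the sample size serves one undefined overall success rate, and no stated rule says which result establishes non-inferiority

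*Protocol article*

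**What the plan says.** The abstract (Methods/design) gives every visit and both measures the same rank: "The primary outcomes that will be assessed are clinical and radiographic success after six-months, one-year and two-years of the trial interventions".

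The body of the article spreads the same content over several sections:

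- Follow-up timeline lists the visits without singling one out: "Clinical and radiographic outcome data of the treated tooth will be recorded at 6 months, 12 months, and 24 months post-treatment".
- Primary outcomes defines the two measures separately and names no visit. Clinical success "of the treated tooth will be determined if all the following conditions are met"; radiographic success begins with "Absence of pathosis on recall periapical radiograph". No composite of the two is defined.
- Objectives frames the comparison as "based on the clinical and radiographic outcomes of the treated teeth over a two-year period".
- Target sample size treats the trial as having one binary outcome: "a 95% success rate was assumed for both treatment interventions along with a 17% non-inferiority margin". It then adds: "Even an overall success rate of 78% for the experimental pulpotomy intervention would be considered non-inferior". This is the only place where an overall rate appears, and neither its components nor its time point is given.
- Statistical methods applies logistic regression to every outcome and a two-sided 0.05 level to every test. It gives no order among the outcomes and no rule for combining them.

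**The concern.** A non-inferiority trial ends in a yes or no, and the protocol should say which result decides it. Here six results have equal standing and the planned power belongs to a seventh quantity that is not among them.

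Two things follow. First, if the outcomes disagree, for example margin met on clinical success at six months but not on radiographic success at two years, the document gives no answer. Disagreement is not far-fetched: the Background cites a pulpotomy cohort with 93% clinical and 90% radiographic success at one year. Second, the error rate and the power depend on the missing rule. If one success is enough, the chance of a false claim rises above the level of a single test. If all six must succeed, the power falls below the stated 80%.

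The 95% assumed for sizing also cannot be judged until the outcome is named, because a composite rate may be lower than the rate of either component.

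**Working it through.** **Inputs.** From Target sample size: success 95% in both arms, margin 17 points, power 80%, two-sided α 0.05, 42 in total, raised to 50 (25 per arm). From the abstract: 2 measures × 3 visits = 6 outcomes. The correlation between outcomes is not in the document, so it is assumed and shown as a range.

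**Step 1: the plan's own figure.** With unpooled variance, n per arm = [p₁(1−p₁) + p₂(1−p₂)] × (z_α + z_β)² / Δ². For p₁ = p₂ = 0.95 the bracket is 2 × 0.95 × 0.05 = 0.095, and Δ² = 0.17² = 0.0289.

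- One-sided 5%: 0.095 × (1.645 + 0.842)² / 0.0289 = 20.3, so 21 per arm, 42 in total. This reproduces the stated 42.
- One-sided 2.5% (the usual reading of two-sided 0.05): 25.8, so 26 per arm, 52 in total.

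The stated 42 is therefore the size for one comparison, with no allowance for six. Because the level is ambiguous, both are carried forward.

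**Step 2: any one of six is enough.** Suppose pulpotomy is truly 17 points worse on all six outcomes. Under independence the chance of at least one false claim is 1 − (1 − α)⁶: 1 − 0.975⁶ = 14.1% and 1 − 0.95⁶ = 26.5%. Under perfect correlation it is α itself. Values in between come from a simulation of six equally correlated normal test statistics (400,000 draws).

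**Step 3: all six are required.** Each test is given 80% power. Under independence the joint power is 0.80⁶ = 26%; the other values come from the same simulation and are nearly the same at both levels.

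| Assumed correlation | Any of six, one-sided 2.5% each | Any of six, one-sided 5% each | All six, joint power |
|---|---|---|---|
| 0 (ceiling for error, floor for power) | 14.1% | 26.5% | 26% |
| 0.5 | 10.3% | 18.5% | 48% |
| 0.9 | 5.4% | 9.9% | 68% |

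**Step 4: what a single composite would need.** A tooth that must succeed both clinically and radiographically cannot have a higher success rate than the lower of the two. Take 90% in both arms, borrowed from the one-year radiographic rate of the pulpotomy cohort in the Background. This is an assumption: that figure is for one arm, one year and one component. The bracket becomes 2 × 0.90 × 0.10 = 0.18.

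- One-sided 5%: 0.18 × (1.645 + 0.842)² / 0.0289 = 38.5, so 39 per arm.
- One-sided 2.5%: 0.18 × (1.960 + 0.842)² / 0.0289 = 48.9, so 49 per arm.
- Power with 25 per arm: 0.17 / √(0.18/25) = 2.00. Then Φ(2.00 − 1.645) = 64% and Φ(2.00 − 1.960) = 52%.

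At 95% in both arms, 25 per arm would give 87% and 79%.

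**The case against.** The best defence has four parts.

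*The six-outcome reading rests on one abstract sentence, and the article leans towards two years.* Partly right. The Primary outcomes section names no visit, the timeline is about data collection, and the background, objectives and discussion all point to two years. That makes the fix easy. It does not remove the sentence that ranks all three visits as primary, nor does it say how the two measures combine.

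*Multiplicity rules may sit in an analysis plan that is not shown, and a journal article condenses.* This stands for the detail of any adjustment, so the absence of one is not the point here. Which outcome is primary, and which one the sample size serves, are protocol matters, and this document does state them, in terms that do not fit together.

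*The error figures are artificial.* Largely right. They need true inferiority of exactly the margin on all six outcomes. Repeated assessments of the same tooth will be positively correlated, so the independence figures are ceilings. If pulpotomy truly is within the margin on an early outcome, a claim there is correct for that outcome; the worry is then relevance, which these figures do not measure.

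*A composite costs power.* This stands and is carried into the fix.

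A reader might go further and infer that the investigators may claim non-inferiority on the easiest of the six. The document does not say so: it neither allows nor forbids it, and that rule would be read into silence. Nor does it show that early clinical success is the least sensitive measure. The nearest evidence is the three-point gap at one year in the cited cohort.

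**Conclusion.** The concern holds as a mismatch within the protocol. Six outcomes are primary, the sample size is for one overall rate with no definition, and no stated rule links any result to the non-inferiority conclusion.

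Its size depends on the missing rule. With any of six sufficient and correlations of 0.5 to 0.9, the false-claim chance would be about 5% to 10% at one-sided 2.5% each, or about 10% to 18.5% at the one-sided 5% that reproduces 42. Those are roughly two to four times the level of a single test. With all six required, power would be about 48% to 68%. These ranges rest on equal correlations, a normal approximation and, for the error rates, true differences at the margin throughout. They show what is left open, not the operating characteristics of a rule the protocol has adopted.

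**What to change.** Name one primary outcome: success of the treated tooth at 24 months, defined as meeting both the clinical and the radiographic criteria. This fits the two-year aim and uses data already scheduled for collection. It is a reasonable choice rather than one the text dictates, since the meaning of the overall rate can only be guessed. Make the two components and the 6- and 12-month results secondary, reported with confidence intervals and no non-inferiority claim of their own. Rewrite Target sample size so that its success rate refers to this outcome, with the test level stated. Make the change before outcomes are analysed, in both the protocol and the registry.

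The wording costs little. The real cost is candour about power: if the composite rate were near 90% in both arms, the planned 25 per arm would give roughly 64% (one-sided 5%) or 52% (one-sided 2.5%), against the 39 or 49 per arm needed for 80%. The proposal is to restate the power openly for the named outcome, not to enrol more patients.

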**Discussion:**

This trial seeks to provide evidence on whether pulpotomy treatment can be no worse than the standard pulpectomy treatment for the management of symptomatic irreversible pulpitis in vital primary molars.

**Trial registration:**

ClinicalTrials.gov (NCT06183203). Registered on 30 January 2024.

## Background/rationale

Current guidelines from the American Academy of Pediatric Dentistry (AAPD) and the British Society of Paediatric Dentistry (BSPD) recommend pulpectomy as the standard treatment for vital primary molars diagnosed with irreversible pulpitis [1, 2]. Pulpectomy is a non-vital treatment procedure where the entire pulp tissue is extirpated, and the root canals debrided and shaped to receive a resorbable material to fill the canal space in the affected primary tooth. The main objectives of pulpectomy in painful primary molars are to keep them symptomless and functional, while also preserving the arch space until their exfoliation and replacement by their permanent successors [3]. Treatment indications for the more conservative pulpotomy procedure (where only the coronal pulp tissue is removed), are restricted to vital primary teeth diagnosed with reversible pulpitis or in case of carious/mechanical pulp exposures in symptomless vital primary teeth [1].

Traditionally, the clinical diagnosis of irreversible pulpitis in a deeply carious primary molar was based on patient reported symptoms of spontaneous lingering pain or pain that persists even after the removal of any provoking stimuli. Radiographic examination of such a tooth would reveal carious exposure of the pulp with or without furcal rarefaction. As conventional pulp sensibility tests are not very reliable in primary teeth, the vitality of a primary tooth diagnosed with irreversible pulpitis is usually ascertained intra-operatively after deroofing the pulp chamber, based on the colour and volume of the observed pulp tissue [4]. However, even if the pulp of such a tooth is judged to be vital, radicular pulp is still extirpated based on the clinical diagnosis of irreversible pulpitis. This treatment approach is adopted due to the traditional notion of the poor healing capacity of primary dental pulp [5]. Early histological studies seemed to indicate that primary teeth with a history of spontaneous pain are often associated with extensive degenerative changes extending into the radicular pulp and are poor candidates for vital pulpotomy techniques [6–8]. Another long-established rationale for performing pulpectomy in symptomatic vital primary teeth was the suggestion that primary tooth pulps exhibit a more pronounced and widespread inflammatory reaction to dental caries compared to permanent tooth pulps and hence would be poor candidates for pulpotomy [9].

The 21st century has seen an improved understanding of pulp biology, pulpal inflammatory processes, and the potential for pulp healing and repair. Histopathologic and histobacteriologic studies in cariously exposed “irreversibly” inflamed permanent tooth pulps have found healthy pulpal architecture, free from inflammation and bacteria, few millimetres away from the bacterially colonised necrotic tissue in the pulp chamber [10–12]. If the infected coronal pulp is completely removed, a favourable environment can be created for radicular pulpal healing as the immunoinflammatory cells get eliminated by apoptosis and the odontoblast-like cells induce dentine bridge formation. This contemporary understanding of pulp pathophysiology, along with the introduction of bioactive calcium silicate cements, has revolutionised treatment modalities for the management of irreversible pulpitis in mature permanent teeth, even when they are associated with apical periodontitis [13]. There is now abundant evidence from randomised controlled trials (RCTs) and systematic reviews favouring conservative vital pulp therapy in permanent teeth diagnosed with irreversible pulpitis [14–23].

A corresponding paradigm shift in the treatment approaches to “irreversibly” inflamed vital primary pulps has not been seen despite new evidence emerging regarding primary pulp biology. Immunocytochemical and vascular studies have now established that primary and permanent pulps have similar vascularity and showed a comparable degree of vasodilation and angiogenesis in response to the caries insult [24, 25]. The pulpal tissues in both carious primary and permanent teeth also showed similar neural changes when mounting a defense to deep caries [26]. Furthermore, although primary pulp tissue contains more immune cells in both normal and carious states, these immune cells appear to localize in a manner identical to that seen in permanent teeth pulp tissue [25]. These histological findings suggest the need to re-evaluate treatment approaches to primary dentition pulp therapy similar to what is currently underway within adult endodontics [5]. This is especially important as literature reports also suggest that clinical symptoms, radiographic findings, and conventional pulp sensibility tests do not provide accurate information about pulp status in primary teeth [27, 28].

There are several advantages if pulpotomy can be offered as a substitute to the standard pulpectomy treatment for the management of irreversible pulpitis in vital primary molars. The ribbon-like torturous root canal anatomy in primary molars makes pulpectomy a difficult procedure for general dentists to perform, often requiring a child in pain to be referred to a specialist paediatric dentist for definitive treatment. In many situations, specialist care may not be easily accessible, or parents may not be able to afford its costs. Consequently, some parents may opt to extract the painful primary molar tooth of their child, resulting in complications such as the loss of function and arch integrity. The technically simpler pulpotomy procedure is not only less challenging for general dentists but is also potentially less time-consuming and easier for young patients to tolerate, both very important advantages in the dental treatment of children. Moreover, the pulpotomized primary tooth retains the regenerative/repair potential of the remnant radicular pulp and the proprioceptive sensation of the tooth. Finally, treatment complications sometimes associated with pulpectomy (e.g., extrusion of root filling material beyond the primary root apex) can be avoided if pulpotomy is the treatment of choice.

There is limited research on whether pulpotomy can be offered as an alternate treatment to pulpectomy in vital primary molars diagnosed with irreversible pulpitis. A prospective cohort study of pulpotomy in 50 vital primary teeth with irreversible pulpitis reported 93% clinical success and 90% radiographic success after one year of treatment [29]. A more recent retrospective study found higher clinical success rates for pulpotomy (99%) than pulpectomy (88%) in primary molars with carious pulp exposures or symptomatic irreversible pulpitis over an 18-month period [30]. To the best of our knowledge, there have been no RCTs comparing treatment outcomes of pulpotomy vs. pulpectomy for management of irreversible pulpitis in vital primary molars. This study aims to fill this research gap and could be of great importance in initiating a paradigm shift in the treatment of vital primary molars diagnosed with irreversible pulpitis. The objectives and hypothesis of the study are detailed below.

### Objectives

Compare the treatment effectiveness of full pulpotomy vs. single-visit pulpectomy in the management of vital primary molars diagnosed with symptomatic irreversible pulpitis based on the clinical and radiographic outcomes of the treated teeth over a two-year period.Assess influence of baseline pre-operative variables (age; gender; tooth type; site of caries; pre-operative furcal radiolucency; pre-operative pain intensity) and intra-operative factors (time taken to achieve haemostasis) on treatment outcomes.

### Hypothesis

The null hypothesis of the study is that the treatment outcomes of the experimental pulpotomy intervention will not be inferior to the highly successful outcomes of the standard pulpectomy treatment for vital primary molars diagnosed with irreversible pulpitis.

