## Methods

### Trial design

This clinical study is a parallel, two-armed, open label, non-inferiority randomised controlled trial with a 1:1 allocation ratio between the experimental intervention arm (pulpotomy) and the active comparator arm (pulpectomy).

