### Statistical methods

All analyses will use the ‘intention to treat’ principle. Baseline demographic and clinical data will be summarised for each treatment group. Binary logistic regression models will be applied to analyse all outcome measures stated in the protocol adjusting for covariates thought to be of prognostic importance. Appropriate parametric or non-parametric tests will be used to determine any significant relationship between treatment outcomes and variables in the study (age, gender, tooth/caries type, and pre-operative furcal rarefaction/pain intensity). For all statistical tests, we will use 2-sided *p*-values with α ≤ 0.05 and the treatment effect estimates will be presented with 95% confidence intervals. Up-to-date versions of SPSS (Chicago, IL, USA) will be used to conduct the statistical analysis.

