## Discussion

The proposed study is unique in that for the first time a non-inferiority RCT is evaluating whether the experimental pulpotomy treatment can prove to be no worse than the standard pulpectomy treatment for the management of symptomatic irreversible pulpitis in vital primary molars. Considering that pulpotomy has been shown to have highly successful treatment outcomes in vital mature permanent molars diagnosed with irreversible pulpitis, there exists the possibility of similar successful outcomes in primary molars too. Consequently, this trial has the potential to produce new knowledge and add information to an area that is currently under researched.

It is important to highlight that the root filling material proposed to be used in the pulpectomy intervention group (Endoflas) has among the highest success rates reported for primary root canal filling materials [31–35]. Similarly, the new generation MTA product proposed to be used in the pulpotomy intervention group not only retains the biocompatibility, immunomodulatory, osteogenic, and sealing properties of traditional MTA, but being a resin-free pre-mixed bioceramic has superior handling characteristics, faster washout and setting times [36, 37]. The NaOCl proposed to be used as the haemostatic/disinfection agent in the pulpotomy intervention group demonstrated comparable clinical/radiographic success to traditional pulpotomy medicaments like formocresol and ferric sulphate without their drawbacks [38–40]. The two-year follow-up period proposed in this study should be adequate to assess treatment success of the trial interventions in primary molar teeth. Studies with longer follow-up periods can be planned based on the initial results of this study.

If the hypothesis of the proposed study is confirmed, it will support the clinical application of more conservative treatment approaches to vital primary teeth with irreversible pulpitis. Such an approach has the potential to cause less pain and discomfort to paediatric patients, have a shorter chair-time, and lower the technical difficulty and cost of managing complicated pulp conditions in vital primary molars.

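### The null hypothesis is stated the wrong way round, against the trial's own non-inferiority design and 17-point margin, so a non-significant difference could be read as non-inferiority

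*Protocol article*

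**What the plan says.** All places are in the protocol article.

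- Hypothesis: "The null hypothesis of the study is that the treatment outcomes of the experimental pulpotomy intervention will not be inferior" to pulpectomy. No margin appears there and no alternative hypothesis is given.
- Trial design: a "non-inferiority randomised controlled trial with a 1:1 allocation ratio".
- Target sample size: "a 95% success rate was assumed for both treatment interventions along with a 17% non-inferiority margin", with "a 2-sided α equal to 0.05" and 80% power. A pulpotomy success rate of 78% is named as the lowest that would still count as non-inferior. The result is about 42 patients in total, raised to 50 teeth for attrition.
- Statistical methods: logistic regression for all outcomes and two-sided p-values "with α ≤ 0.05 and the treatment effect estimates will be presented with 95% confidence intervals". The 17-point margin is not mentioned.
- Discussion: "If the hypothesis of the proposed study is confirmed, it will support the clinical application of more conservative treatment approaches".

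**The concern.** A hypothesis test can reject its null but cannot establish it. If non-inferiority is the null, the trial can only fail to reject it, and a small trial fails to reject easily. The design and sample size assume the opposite: that the data must rule out a deficit of 17 points or more.

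Nothing else in the article corrects the reversed null, and two sections fit it. Statistical methods tests for a difference without the margin. The Discussion refers to the hypothesis being confirmed, and the only hypothesis the article states is this null. A reader following these sections literally could conclude non-inferiority from p > 0.05. The chance of wrongly endorsing pulpotomy would then be the type II error of a small difference test, not the 2.5% that a two-sided 95% interval is meant to allow.

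**Working it through.** **Inputs (Target sample size).** Success 95% in both arms; margin 0.17; power 80%; 42 teeth before attrition (21 per arm) and 50 after (25 per arm). Implied attrition is 1 − 42/50 = 16%.

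**1. The plan's own figure.** Unpooled normal approximation for non-inferiority of two proportions:

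n per arm = (z₁₋α + z₁₋β)² × [p_E(1 − p_E) + p_C(1 − p_C)] / margin²

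The variance term is 2 × 0.95 × 0.05 = 0.095, and 0.095 / 0.17² = 3.287.

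- One-sided 0.05: (1.645 + 0.842)² × 3.287 = 20.3, so 21 per arm and 42 in total. This matches the article.
- One-sided 0.025, equivalent to the stated two-sided 0.05: (1.960 + 0.842)² × 3.287 = 25.8, so 26 per arm and 52 in total. This does not match.

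The sample size is therefore built on the correct null (inferiority by the margin), but at a laxer alpha than the article states.

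**2. If a non-significant difference test were read as non-inferiority.** Let x and y be the successes out of n in the pulpotomy and pulpectomy arms. Sum over all pairs:

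P(endorse) = Σₓ Σ_y Bin(x; n, p_E) × Bin(y; n, p_C) × 1[two-sided p > 0.05]

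Pulpectomy is held at 95%.

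| True pulpotomy success | n per arm | Pearson | Fisher |
|---|---|---|---|
| 78% (at the margin) | 21 | 0.626 | 0.762 |
| 78% (at the margin) | 25 | 0.547 | 0.737 |
| 70% (beyond the margin) | 21 | 0.383 | 0.524 |
| 70% (beyond the margin) | 25 | 0.292 | 0.451 |

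Hand check by normal approximation, 78% v 95%, n = 25. The pooled rate is 0.865, and √(2 × 0.865 × 0.135) = 0.483. The unpooled term is √(0.95 × 0.05 + 0.78 × 0.22) = 0.468. Then z = (0.17 × √25 − 1.960 × 0.483) / 0.468 = −0.21, giving power 0.42 and a non-significance probability of 0.58. At n = 21 the same formula gives 0.64. Both agree with the Pearson column to within 4 points.

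**3. Under a margin rule.** Replace the indicator by 1[lower limit of the two-sided 95% CI for p_E − p_C > −0.17]. At 78% v 95%:

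| n per arm | Newcombe interval | Simple Wald interval |
|---|---|---|
| 21 | 0.023 | 0.046 |
| 25 | 0.022 | 0.037 |

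**4. Power of the margin rule when both arms truly succeed at 95%.** Normal approximation: Φ(0.17 / √(0.095/n) − 1.960).

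- n = 21: 0.17 / 0.0673 − 1.960 = 0.57, power 71%.
- n = 25: 0.17 / 0.0616 − 1.960 = 0.80, power 79%.
- At one-sided 0.05 and n = 21: 2.53 − 1.645 = 0.88, power 81%.

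By exact enumeration, the Newcombe interval at two-sided 95% has power 46% (n = 21) and 57% (n = 25).

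**The case against.** The strongest defence is that the intent is plain. The abstract, Trial design, Target sample size and Discussion all describe a non-inferiority trial, and the margin and the 78% floor are fixed in advance. Statistical methods promises 95% confidence intervals, which is what a margin-based conclusion needs. An analysis plan that is not shown may well tie the interval to the margin, and an article need not carry that sentence.

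Much of this stands. A reader might infer that the investigators will take p > 0.05 as proof of non-inferiority. The documents do not say so, and the Discussion sentence is loose prose rather than a decision rule. A reader might also take the two-sided 0.05 level as part of the error. It is not: a two-sided 95% interval compared with the margin is a standard non-inferiority analysis.

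The probabilities need care too. They apply only if the mistaken reading is used. At 70% v 95% with 25 per arm, Pearson's test would detect the deficit about 71% of the time (1 − 0.292), so it is not true that every difference test usually misses a deficit beyond the margin. The article also words 78% as still acceptable, so the 70% rows are the clearer case of a wrong endorsement. Wald p-values from logistic regression would give higher non-significance rates. Those depend on how tables with no failures in an arm are handled (the pulpectomy arm alone has none with probability 0.95²⁵ = 28% or 0.95²¹ = 34%), so they are not relied on here.

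The defence does not rescue the Hypothesis section. An analysis plan with the correct rule would contradict the published null, so that sentence needs correcting either way.

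**Conclusion.** The point holds as a misstated hypothesis. The published null is reversed, carries no margin, and contradicts the trial's design and sample size. The consequence is a risk, not a stated rule: a non-significant difference could be read as non-inferiority. If it were, the chance of endorsing pulpotomy would be about 55–76% at the margin and about 29–52% at 70% v 95%, across Pearson and Fisher tests and 21 to 25 per arm. Under a 95% interval rule the chance at the margin is about 2–5%.

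These figures assume one binary success outcome at one time point, unadjusted tests, independent teeth and a true pulpectomy success of 95%. The adjusted logistic analysis was not simulated.

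**What to change.** 1. In Hypothesis, write: H0: success(pulpotomy) − success(pulpectomy) ≤ −17 percentage points; H1: the difference is greater than −17 points.
2. In Statistical methods, add that non-inferiority is concluded only if the lower limit of the two-sided 95% CI for the risk difference lies above −17 points, and that a non-significant difference test is not evidence of non-inferiority. Logistic regression yields odds ratios, so if the primary analysis is adjusted, obtain the risk difference from the model by standardisation. Name the interval method.
3. In Target sample size, reconcile alpha with the rule and restate the power.

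Steps 1 and 2 are a few sentences in the protocol and registry entry and change no treatment or data collection. Step 3 has a real cost. With the two-sided 95% rule, 80% power needs 52 evaluable teeth, or 52 / 0.84 = 62 enrolled at the same 16% attrition. If the target stays at 50, the protocol should state power of about 71% (21 per arm) to 79% (25 per arm) by normal approximation, or about 46% to 57% if a Newcombe interval is used. Keeping 42 teeth at 80% power would mean declaring one-sided 0.05 openly, which conflicts with the two-sided 0.05 now stated. The choice should be made and dated before outcomes are known.
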